#### Quality of life

We will obtain QoL data from a representative sample of patients undergoing AAA surgery during the study period. This will equate to 800 patients. We expect a 50% loss to follow-up, through non-compliance and natural attrition from death during the follow-up period. We plan to obtain QoL from 300 medically managed patients. Three hundred patients will give a 95% CI of maximum width 12.5 for the difference in mean EQ-5D-5L Visual Analogue Scale (EQ-VAS) values between baseline and later time points based on an SD equal to 20. The SD was calculated after an evaluation of EQ-VAS scores across a wide range of trials.

### Data analysis plan

Analyses will be carried out on an intention-to-treat basis, retaining all patients in the surgery group to which they are assigned irrespective of any procedural issues. The intervention groups will be OSR, FEVAR, EVAR±adjuncts (including chimneys and endoanchors). The exact treatment received will be determined by triangulation of NVR data and HES data for OSR. Patients receiving endovascular treatment will be identified from NVR data and HES data, and exact technical details of each procedure (including the use of adjuncts) will be determined through analysis of procedural images in the Corelab.

As an analysis of observational cohort data, all attempts to present a measure of efficacy free from confounding bias will be undertaken. Patients will be stratified by infrarenal neck length for analysis into three groups: 0-4 mm (juxtarenal), 5–9 mm (juxtarenal) and ≥10 mm neck length (not juxtarenal but complex based on device-specific IFU criteria). This will serve to limit anatomical heterogeneity and bias within comparisons. Additionally, patients will be stratified by physiological risk. The British Aneurysm Repair Score^23^ will be used (11 clinical parameters available from NVR data) to divide each comparison group into those that are high risk (the highest risk quartile) and the remainder as standard risk.

Statistical analyses of the primary outcome shall follow the principle of propensity score analysis. Propensity score estimation is chosen for the analysis of the primary endpoint instead of multivariable regression techniques because it is considered the most appropriate means of accounting for selection bias at the low level of perioperative death rates anticipated.^24^ Propensity scores estimate the probability of a patient being given each treatment strategy based on baseline clinical and demographic characteristics. Patients can then be stratified based on their propensity to receive each treatment strategy and an estimate of treatment effect is then obtained, which adjusts for potential selection bias in the data.

Models to estimate the propensity for each patient shall be generated using multivariable logistic modelling techniques using as candidate covariates only variables that influence simultaneously the treatment assignment and the outcome variable. Covariates shall be retracted to demographic/clinical data available at the point of treatment decision with the aim of producing a propensity model that satisfies the assumptions of conditional independence. The final analysis shall be carried out using stratified logistic where the strata are defined by the quintiles of the fitted propensity score values. Prior to analyses, it shall be confirmed that each stratum contains at least 20 observed perioperative deaths. If not, the strata will be combined with an adjacent strata level.

The key efficacy parameter of interest will be an OR presented with a 97.5% CI. Results will be presented as a forest plot with the OR within each stratum presented along with the overall effect.

Reports of HES data validation confirm high levels of completeness and accuracy. Therefore, missing data or inaccurate data are unlikely to be a significant problem. It is proposed that covariates with small amounts of missing data (≤10%) will be included on a complete case basis and covariates with a large amount of missing data (>10%) will be excluded from the analysis.

Sensitivity analyses are carried out to ensure the results are not sensitive to either the propensity model or the method of matching. With respect to the propensity model, sensitivity analyses shall be carried out by removing each covariate included in calculating the propensity score and repeating the analysis of the primary endpoints. The results of all sensitivity analyses shall be presented in a forest plot along with the overall effect from the primary analysis.

It is recognised that recruitment for site-reported QoL data will occur either side of a cessation of elective services in the UK due to the COVID-19 pandemic in 2020/2021. There may be differences in patient behaviour and clinical practice before and after this period and we aim to investigate this further in the analysis phase. First, outcome data before and after the dates of interest will be compared. Second, clinical practice before and after the dates of interest will be compared using data from the NVR.

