Endovascular treatments are associated with greater cost than OSR due to the cumulative costs of the stent-grafts, ancillary devices, postoperative surveillance and re-intervention. National Health Service (NHS) clinical service commissioners have noted an increasing demand for FEVAR in the absence of evidence regarding clinical effectiveness identifying which patients would benefit from this procedure and whether the substantial cost associated with the technique is an appropriate use of NHS resources. Prohibitive cost and lack of experience with FEVAR in many arterial centres have concomitantly led to a substantial use of off-label standard EVAR in complex neck anatomy, an intervention that is known to have poorer long-term results compared with on-label EVAR.^17^ The National Institute for Health Research Health Technology Assessment (NIHR HTA) Programme has commissioned this comparative research study in order to resolve this NHS decision problem.

The primary aim of UK COMPlex AneurySm Study (UK-COMPASS) is to answer the research question identified by the NIHR HTA Programme: ‘What is the clinical and cost-effectiveness of strategies for the management of juxtarenal AAA, including fenestrated endovascular repair?’ The five objectives of this study are shown in table 1.

**Table 1 T1:** The UK-COMPASS objectives

Objective 1	To compare different treatment strategies for their perioperative mortality and morbidity, corrected for confounding physiological and anatomical characteristics, in order to account for baseline risk and indication biases.
Objective 2	To identify whether particular physiological and/or anatomical baseline characteristics are associated with better clinical outcomes or better health economic efficiency using one or other treatment strategies.
Objective 3	To compare different treatment strategies in terms of overall survival and in terms of treatment failure in the long-term follow-up (stent-graft-related complications, secondary interventions, aneurysm-related mortality).
Objective 4	To perform cost-effectiveness analyses from NHS and personal social care perspective to establish incremental cost-effectiveness ratios, comparing different treatment strategies in terms of cost per incremental gain in and quality-adjusted life years.
Objective 5	To establish the clinical and cost utility of FEVAR and alternatives, in patients who are considered physiologically unfit for OSR, and to compare these against medical management.

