#### Stratified comparative analysis for perioperative mortality and identification of risk factors

Based on the best available estimates, it is anticipated that 120 events (perioperative deaths) will be available if 2000 patients are included in the study. The aim is to identify anatomical/physiological characteristics for which there is a differential effect on patient outcome depending on the treatment strategy employed. We plan to use multivariable models which include propensity scores as continuous covariates, adjusted for appropriate confounding variables and including interaction effects with treatment effect. Using the statistical rule of thumb of 10 events per variable, approximately 12 variables can be included in any single model. If, for example, a two-level factor is to be investigated, main effects and interaction effects and a covariate of propensity scores will account for six variables, allowing for a further inclusion of other confounding variables as required.

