### Health economic analysis

The UK-COMPASS will adapt the recent National Institute for Health and Care Excellence (NICE) health economic analysis model^25^ which will facilitate updates of NICE Clinical Guideline ‘Abdominal Aortic Aneurysm–Diagnosis and Management (NG156)’.

Our aim is to inform NICE decision-making in a timely manner. The NICE health economic model has been developed from a UK NHS and Personal Social Services perspective, appraised by a NICE committee and scrutinised during consultation, and we see this fit to be adapted without developing a de novo model.

The purpose of the health economic analysis in this study is defined in the original objectives 4 and 5. The main outputs therefore will remain (a) estimation of incremental cost-effectiveness ratios comparing different treatment strategies in terms of life years and quality-adjusted life years gained, and (b) to identify whether particular level of physiological fitness (stratified into two groups) and/or anatomical baseline characteristics (stratified into three groups) are associated with better health economic efficiency using one or other treatment strategies.

At least 5-year follow-up is considered the essential minimum to capture attrition of treatment utility and accrual of treatment costs that occur from late failure/secondary intervention and postoperative surveillance.

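### The protocol's only stated use of the British Aneurysm Repair Score is a top-quartile split; the treatment-by-risk test for Objective 2 should use the continuous score

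*Protocol article*

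**What the plan says.** Objective 2 (Protocol article, Introduction, Table 1) is "To identify whether particular physiological and/or anatomical baseline characteristics are associated with better clinical outcomes or better health economic efficiency" under one or other strategy. The sample size subsection on stratified comparative analysis gives the clinical side of it: "The aim is to identify anatomical/physiological characteristics for which there is a differential effect on patient outcome depending on the treatment strategy employed". It plans multivariable models with treatment interactions, expects 120 deaths in 2000 patients, and sets a budget: "Using the statistical rule of thumb of 10 events per variable, approximately 12 variables can be included in any single model". Its illustration is that if "a two-level factor is to be investigated, main effects and interaction effects and a covariate of propensity scores will account for six variables".

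The Data analysis plan gives the one stated role of the British Aneurysm Repair Score, which is to "divide each comparison group into those that are high risk (the highest risk quartile) and the remainder as standard risk". The Health economic analysis carries the two groups into the economic side of Objective 2, asking whether a "particular level of physiological fitness (stratified into two groups") goes with better efficiency under a given strategy. No reason is given for cutting at the 75th centile. No interaction effect size, alpha or power is stated for Objective 2.

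**The concern.** The score is numeric. After the split, a patient just below the 75th centile counts the same as the fittest patient in the cohort. The boundary is set by rank, not by where the treatment effect is thought to change.

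Objective 2 is a question about interaction, and interactions are imprecise with few events. At the plan's own rates, FEVAR v OSR with 667 per arm gives about 667 × 0.08 + 667 × 0.04 = 80 deaths. If risk modifies the treatment effect gradually, dichotomising discards information that the study already holds. A real gradient could then be missed, or reported only as two stratum odds ratios.

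**Working it through.** **The plan's own figures.**
- OR for 8% v 4%: (0.04/0.96)/(0.08/0.92) = 0.479 (stated 0.48).
- Power for 667 v 667 at two-sided alpha 0.025, normal approximation: 79.9% (stated as above 80%; agrees to rounding).
- Variable budget: 2000 × 6% = 120 deaths; 120/10 = 12 variables.
- Two-level factor with three treatments: 2 treatment + 1 factor + 2 interaction + 1 propensity = 6, as stated.

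**Information kept by the cut.** Assume a normal score with a linear effect on the log odds, which the documents neither state nor exclude. A cut placing a fraction q in the high group keeps φ(z)²/[q(1−q)]. With q = 0.25, z = 0.674 and φ(z) = 0.318, this is 0.101/0.1875 = 0.539. About 54% is kept and 46% lost.

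**Power by approximation.** Multiply the noncentrality (z for alpha + z for power) by √0.539 = 0.734. For 80% power at two-sided 5%: (1.96 + 0.84) × 0.734 = 2.06, and Φ(2.06 − 1.96) = 54%.

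| Power with continuous score | 40% | 50% | 60% | 70% | 80% | 90% |
|---|---|---|---|---|---|---|
| Power with cut, alpha 0.05 | 24% | 30% | 37% | 45% | 54% | 66% |
| Loss (points) | 16 | 20 | 23 | 25 | 26 | 24 |

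At alpha 0.025 the losses over the same range are 18 to 29 points.

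**Power by simulation.** Logistic outcome, normal score, 667 v 667, marginal mortality 8% v 4%, likelihood-ratio test of interaction at 5%, 600 replicates (Monte Carlo error about 2 points). The OSR slope is a log OR of 0.5 or 0.8 per SD. The true interaction is linear, and entries are continuous v cut.

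| Interaction, log OR per SD | OSR slope 0.5 | OSR slope 0.8 |
|---|---|---|
| −0.3 | 20% v 16% | 22% v 13% |
| −0.4 | 39% v 24% | 34% v 23% |
| −0.5 | 50% v 33% | 51% v 37% |
| −0.6 | 68% v 45% | 66% v 48% |
| −0.7 | 78% v 53% | 75% v 57% |

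The loss is about 11 to 25 points for −0.4 to −0.7, and about 5 to 9 points at −0.3, where power is low either way. A separate simulation (OSR OR 2.46 per SD; FEVAR 1.65, 1.49, 1.35, 1.22; Wald test, 2000 replicates) gave 36/49/66/78% continuous v 22/32/44/56% cut, a loss of 14 to 22 points. If endovascular patients are assumed to score 0.5 SD higher, the loss is about 11 to 17 points.

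**The opposite case.** If the true interaction is a step exactly at the 75th centile, the same simulation gives the cut a gain of about 4 to 21 points. For a normal score, the squared correlation of each term with a step shows how far this extends. For a step at the median the cut keeps 0.125²/(0.1875 × 0.25) = 33%, against 64% for the linear score. The cut is better only for steps between roughly the 65th and 90th centiles.

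**Variable count.** Linear score: 2 + 1 + 2 + 1 = 6, the same as the two-level factor. A 3-knot spline: 2 + 2 + 4 + 1 = 9 of 12.

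**The case against.** The strongest reply is that the protocol never says the cut score is the interaction term for clinical outcomes. The two-level factor is offered only as an example of counting variables, the score is not named there, and the functional form of a covariate is often left to the analysis plan. This stands in part: a reader might infer that the document commits the clinical model to the dichotomised score, and it does not do so expressly. What remains is that the split is the only use of the score the document states, that the economic part repeats it for Objective 2, and that nothing points to a continuous term.

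The second reply is that the power loss depends on a score distribution, an effect shape, an interaction size and an alpha that the documents do not give, and that it reverses for a step near the cut. This is correct. The loss has to be stated as conditional.

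A reader might also infer that odds ratios within the standard-risk group are left confounded, because fitter patients tend to receive OSR. The documents do not support that. The plan also adjusts by propensity quintiles in the primary analysis and by a continuous propensity covariate with other confounders in the interaction models.

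Nor does the same argument carry over to neck length. The Data analysis plan ties its 10 mm boundary to device instructions for use. Table 2 admits patients below 10 mm on length alone, but those at 10 mm or more only with another adverse neck feature. A linear term in millimetres would run across that change in eligibility.

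**Conclusion.** The concern holds in a limited form. Read as written, the physiological effect-modification analysis rests on a top-quartile split. The cut keeps about 54% of the information if the score is roughly normal and acts linearly on the log odds. It costs roughly 10 to 25 points of interaction power under moderate linear interactions with 667 per arm, 8% v 4% mortality and two-sided 5%. The loss is smaller for weak interactions and becomes a gain if the effect is a step near the 75th centile, for which the document gives no evidence.

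The primary odds ratio for perioperative death is not affected. The point also does not depend on whether the quartile is taken within each comparison or over the whole cohort. It is an avoidable loss of precision on a stated objective.

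**What to change.** In the Data analysis plan and in the sample size subsection on stratified comparative analysis:
- State that the primary treatment-by-physiological-risk test uses the continuous British Aneurysm Repair Score, for example on the logit scale, with a linear interaction term and a spline as a check on shape.
- Report the treatment effect across the range of the score.
- Keep the high and standard risk groups for display and for the health economic subgroups.
- Keep the three neck-length groups.

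If a continuous term is already intended, one sentence saying so is enough. The cost is wording only, with no new data and the same six variables. The small downside is that linearity must be checked, and a 3-knot spline raises the count to 9 of the 12 available.

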### Sample size calculations

#### Perioperative mortality

The primary outcome measure is perioperative death. The primary efficacy parameter is the OR comparing FEVAR with both open repair and off-label EVAR. For OSR, conservative estimate of 8% perioperative death might be expected, and a reduction to 4% could be considered clinically relevant, which is equivalent to an OR of 0.48 (based on NVR 2015 report^21^ and GLOBALSTAR registry^22^). This effect is slightly larger than that noted in randomised controlled trials of standard infrarenal aneurysm repair.^5^ A Bonferroni adjusted two-sided alpha level of 0.025 is used. Based on these assumptions, collecting data on 2000 patients will ensure a power in excess of 80% if the allocation between treatments is relatively equal and should be preserved above 70% even if one treatment strategy is used twice as much as the other two.

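### The protocol names the centre as a reason for FEVAR or off-label EVAR, but the primary propensity analysis takes no account of centre in the odds ratio, its interval or the sensitivity analyses

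*Protocol article*

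**What the plan says.** The Introduction gives a centre-level reason for the choice between two of the compared repairs: "Prohibitive cost and lack of experience with FEVAR in many arterial centres have concomitantly led to a substantial use of off-label standard EVAR". FEVAR versus off-label EVAR is one of the two primary comparisons under Sample size calculations, the other being FEVAR versus open repair.

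The Data analysis plan defines the propensity score from patients' clinical and demographic characteristics. Candidate covariates must influence both treatment and outcome, and the stated goal is conditional independence. It then restricts the set: "Covariates shall be retracted to demographic/clinical data available at the point of treatment decision" (the second verb presumably means restricted). The primary model is fixed as well: "The final analysis shall be carried out using stratified logistic where the strata are defined by the quintiles of the fitted propensity score values". The result is an OR with a 97.5% CI. The further stratifiers, neck length and the British Aneurysm Repair Score, are patient-level.

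The sensitivity analyses drop propensity covariates one at a time and vary the matching method. Neither the primary model nor these analyses mention centre, centre volume or clustering.

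**The concern.** A variable that the protocol itself describes as steering treatment stays outside the adjustment. If centres that favour FEVAR also differ in perioperative mortality for reasons unrelated to the type of repair, part of the primary OR belongs to the hospital and not to the operation. Propensity quintiles built from patient characteristics cannot remove that part.

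A second, smaller issue is precision. Patients in one hospital share surgeons, critical care and habits of selection. If repair type is also concentrated by hospital, a model that assumes independent patients can give too short an interval.

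The stakes are practical. The study was commissioned to tell NHS commissioners whether FEVAR's cost is justified, and its results feed an adapted NICE model. Strengths and limitations concedes only that unknown biases may remain; the link from centre to treatment is known and stated.

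**Working it through.** **The plan's own figure.** Inputs from Sample size calculations: "A Bonferroni adjusted two-sided alpha level of 0.025 is used"; "conservative estimate of 8% perioperative death might be expected, and a reduction to 4% could be considered clinically relevant"; "collecting data on 2000 patients will ensure a power in excess of 80% if the allocation between treatments is relatively equal".

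- OR = (0.04/0.96)/(0.08/0.92) = 0.479, matching the stated 0.48.
- With 2000/3 ≈ 667 per group, 8% versus 4% and two-sided alpha 0.025, the normal-approximation power is 79.9%. The stated power is thus reproduced to rounding, with independent patients and no centre effect.

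The document gives no centre count, intracluster correlation (ICC) or between-centre spread. Everything below rests on assumed values.

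**Possible bias, FEVAR versus off-label EVAR, true OR = 1.** Assume two equally large types of centre. FEVAR makes up 70% of the two repairs in type A and 30% in type B, and mortality depends only on centre type.

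- A 5%, B 7%: FEVAR deaths 0.7×5 + 0.3×7 = 5.6%; off-label deaths 0.3×5 + 0.7×7 = 6.4%. Apparent OR = (0.056/0.944)/(0.064/0.936) = 0.87.
- A 4%, B 8%: 5.2% versus 6.8%, apparent OR = 0.75.
- With A and B mortality exchanged, the ORs invert: 1/0.868 = 1.15 and 1/0.752 = 1.33.

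**Simulation with no true effect.** 1333 patients per comparison, 40 or 75 centres, between-centre SD in outcome of 0.3 to 0.7 on the log odds, several strengths of centre preference, Mantel-Haenszel OR over quintiles of a patient covariate.

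| Centre preference and centre outcome | OR ignoring centre | Other results |
|---|---|---|
| Correlated (−0.5) | 0.63 to 0.91 | coverage of the nominal 97.5% CI 63% to 97%; OR about 1.0 to 1.08 when also stratified by centre |
| Uncorrelated | about 1.0 | true SD exceeds model SE by about 0% to 27% |

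Bias therefore needs the two to be correlated. The minus sign was chosen for illustration; a positive correlation would push the OR above 1.

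**Interval width, upper bound.** Suppose that centre alone decides the repair. Design effect = 1 + (m − 1)×ICC, where m is patients per centre.

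- 80 centres, ICC 0.005: m = 1333/80 = 16.7; 1 + 15.7×0.005 = 1.08; width factor √1.08 = 1.04; true coverage 96.9%.
- 40 centres, ICC 0.02: m = 1333/40 = 33.3; 1 + 32.3×0.02 = 1.65; width factor √1.65 = 1.28; true coverage 91.9%.

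Dividing 667 by the unrounded design effects (1.078 and 1.647) gives effective group sizes of about 618 and 405, and power of 76.5% and 56.2%. The simulation, where repair is not wholly decided by centre, reaches from no effect to about this upper bound.

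**The case against.** A reader might infer that the primary ORs do mix repair with hospital, that FEVAR will be flattered, and that the interval is certainly too tight. The document supports none of these as fact. It reports no centre-level mortality. That centre affects how well a repair is done is an inference from the remark about lack of experience, and the direction of any bias is unknown. Interval error is negligible when repair choice is only weakly tied to centre.

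It is also fair that the centre statement concerns FEVAR against off-label EVAR. For open against endovascular repair, the Introduction points to physiological fitness, which the plan does address through the risk score and propensity score. The concern is correspondingly weaker there.

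The covariate restriction can be read chiefly as a timing rule that keeps out post-decision variables. Variance estimation is often left to an analysis plan, and an article condenses. The section on stratified analysis and risk factors does allow further confounders, but for that analysis and not for the primary model.

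What remains is more than silence. The article fixes the class of covariates, the primary model and the list of sensitivity analyses, and following them as written leaves out a treatment determinant that the same article names.

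The objection also limits the remedy. FEVAR volume is zero where no FEVAR is done, so it nearly determines treatment and would damage overlap. The expected 120 deaths over an assumed 40 to 80 centres are 3 to 1.5 per centre, too few for many centre fixed effects.

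**Conclusion.** The point holds in a conditional form. Centre is a stated determinant of FEVAR or off-label EVAR, and the primary analysis as written does not account for it. Whether this biases the OR depends on a link between centre and perioperative death that is plausible but undocumented. If that link exists and runs with centre preference, shifts of a null OR to about 0.87 or 1.15 follow from modest assumptions, and to 0.63 or lower-to-mid 0.9s across the simulated settings, against a design target of 0.48. The sign cannot be known in advance. The correct 97.5% CI would be from negligibly to roughly a quarter wider. Bias is the larger of the two worries. All sizes rest on assumed centre counts, spreads and preferences. This is an amendment that should be made; it does not invalidate the design.

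**What to change.** In the Data analysis plan:

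1. Report the primary OR and its 97.5% CI with centre-clustered variance, or from a model with a centre random intercept. Clustered variance corrects the interval but not bias, so item 2 is needed as well.
2. Pre-specify one sensitivity analysis that accounts for centre. Either restrict it to centres performing both compared repairs, with a centre random effect or a centre-conditional model, or adjust for overall centre AAA or complex-repair volume. Do not use FEVAR volume for this.
3. State that the treating-centre identifier from NVR/HES is kept in the pseudonymised analysis data. Scans are retrieved from provider sites, so treating hospitals should be traceable, but the article does not say that the identifier reaches the analysts.

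Cost: wording and modest extra analysis, with no new clinical data if the identifier is available. Intervals will be somewhat wider, and the within-centre analysis will be imprecise with about 120 deaths across all arms. It should be presented as a check on direction and size, not as a second test.

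### The rule merging propensity quintiles with fewer than 20 deaths will probably leave fewer than five strata, letting outcome counts coarsen the primary adjustment for little gain

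*Protocol article*

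**What the plan says.** In the Data analysis plan, the primary endpoint is analysed by stratified logistic regression in which "the strata are defined by the quintiles of the fitted propensity score values". Before that analysis it must be confirmed that "each stratum contains at least 20 observed perioperative deaths. If not, the strata will be combined with an adjacent strata level".

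The sample size section makes the primary parameter the odds ratio of FEVAR against open repair and against off-label EVAR. For open repair, a "conservative estimate of 8% perioperative death might be expected, and a reduction to 4% could be considered clinically relevant". The article puts the corresponding odds ratio at 0.48. On size, "collecting data on 2000 patients will ensure a power in excess of 80% if the allocation between treatments is relatively equal", and "A Bonferroni adjusted two-sided alpha level of 0.025 is used".

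The only total given for deaths is in the section on stratified comparative analysis: "120 events (perioperative deaths) will be available if 2000 patients are included in the study". That total covers all treatments. The Methods section on routinely collected data expects about 3000 patients to meet the anatomical criteria. The article does not say whether the quintiles and the 20-death check apply to the whole cohort or to each pairwise comparison.

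**The concern.** The article gives both the threshold and the expected deaths, and the two fit poorly. Each primary odds ratio uses only the deaths in two of the three treatment groups, so the pairwise count falls short of what five strata of 20 deaths require.

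When a stratum falls short, patients with different propensities are put together and more confounding remains within the merged stratum. The trigger is the observed outcome, whereas a propensity design is meant to be settled without it. The article prefers propensity methods to multivariable regression because deaths will be few. This rule then lets the small number of deaths weaken the propensity adjustment.

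**Working it through.** **Inputs.** From the article: 2000 patients; mortality 8% (open repair) and 4% (FEVAR); two-sided alpha 0.025; 120 deaths in all; about 3000 eligible patients; five strata; at least 20 deaths each. Assumed: EVAR mortality, which is not stated, is 4% to 8% (6% reproduces the total of 120); the spread of deaths across quintiles; and the confounding strengths in step 4.

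**1. The plan's own figures.** Odds ratio: (0.04/0.96)/(0.08/0.92) = 0.479, stated as 0.48. Deaths: 2000 × 6% = 120, or 667 × (0.08 + 0.04 + 0.06) = 120. Power for 667 against 667 at alpha 0.025 is 0.799, close to the stated 80%. All three are reproduced.

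**2. Deaths available against the 5 × 20 = 100 required.**

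| Patients stratified | Expected deaths | Per quintile |
|---|---|---|
| FEVAR v open, N = 2000, equal groups | 27 + 53 = 80 | 16 |
| FEVAR v EVAR, N = 2000, equal groups | 27 + (27 to 53) = 53 to 80 | 10.7 to 16 |
| FEVAR 500 v open 500 | 20 + 40 = 60 | 12 |
| FEVAR 500 v open 1000 | 20 + 80 = 100 | 20 |
| All treatments, N = 2000 | 120 | 24 |
| FEVAR v open, N = 3000, equal groups | 40 + 80 = 120 | 24 |
| FEVAR v EVAR, N = 3000, equal groups | 40 + (40 to 80) = 80 to 120 | 16 to 24 |
| All treatments, N = 3000 | 3000 × 6% = 180 | 36 |

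Complete-case handling of covariates can only lower these counts.

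**3. Chance that all five strata survive.** Binomial simulation, 20,000 runs, five equal-sized strata. A stratum below 20 deaths is merged with its smaller neighbour. The first figure is for evenly spread deaths, the second for a linear twofold gradient across quintiles.

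| Patients stratified | All five survive | Usual result |
|---|---|---|
| FEVAR v open, N = 2000 | about 0.000 in both | two or three strata: 0.98, 0.94 |
| FEVAR v EVAR at 6%, N = 2000 | 0.000, 0.000 | two strata: 0.85, 0.69 |
| FEVAR 500 v open 1000 | 0.04, 0.004 | three strata: 0.52, 0.55 |
| All treatments, N = 2000 | 0.39, 0.07 | four strata: 0.47, 0.75 |
| FEVAR v open, N = 3000 | 0.39, 0.08 | four strata: 0.47, 0.74 |
| FEVAR v EVAR at 6%, N = 3000 | 0.04, 0.004 | three strata: 0.53, 0.55 |
| All treatments, N = 3000 | 0.99, 0.81 | five strata |

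**4. With explicit confounding.** One normal confounder drives both treatment and death. Log-odds slopes on treatment and outcome are 0.7 and 0.5, or 1.0 and 0.7, with either sign for treatment. The true odds ratio is 0.48. With 80 deaths, five strata survived in 0% of runs and the mean number left was 2.4 to 2.7. With 120 deaths in the two-group comparison, five survived in 0% to 2% and the mean was 3.1 to 3.8.

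**5. Confounding left by coarser strata.** For a standard normal confounder with linear effects, the share of bias removed is Σ pⱼmⱼ², where pⱼ is the stratum's share of patients and mⱼ the confounder mean within it. Equal strata remove 89.7% (five), 79.3% (three) and 63.7% (two). The residuals are 10.3%, 20.7% and 36.3%, so residual bias rises by 20.7/10.3 = 2.0 times and 36.3/10.3 = 3.5 times. For strata built by merging quintiles, one merge (four strata) removes 82% to 87%, three strata about 75% to 79%, and a 40/60 split about 62%.

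**6. Effect on the odds ratio, 80 deaths.** The average odds ratio moves from 0.51 (five strata) to 0.53 (after merging) with the weaker slopes, and from 0.52 to 0.58 with the stronger. With the stronger slopes and the treatment slope reversed it moves from 0.44 to 0.39. Each move is away from 0.48. The standard error of the log odds ratio is √(1/53.4 + 1/613.6 + 1/26.7 + 1/640.3) = 0.244. The shifts are ln(0.53/0.51)/0.244 = 0.16, ln(0.58/0.52)/0.244 = 0.45 and ln(0.44/0.39)/0.244 = 0.49 standard errors. Merging did not materially reduce the standard error.

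**The case against.** The strongest reply is that 2000 is the number used for power, not the number expected. The article expects about 3000 patients, all of them included. It speaks of a propensity for each treatment strategy, which allows strata on the whole cohort. Even at 2000 patients, 120 deaths over five strata average 24, so a threshold of 20 may have been chosen with the pooled cohort in mind. This stands in part. A reader might infer that the rule can never be met and that merging is certain, but the article does not support that: strata on the pooled 3000 would probably survive. An average of 24 is not enough, however, because confounding means that deaths concentrate at one end of the score. A twofold gradient cuts the chance of keeping five strata to 0.07 or 0.08.

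A second reply is that the trigger is prespecified, uses total deaths rather than deaths by treatment, and so does not look at the treatment contrast. That is fair, and no inflation of type I error has been shown. Observed deaths still set how finely confounding is controlled.

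A third is that the harm is small against a 97.5% interval of roughly 0.28 to 0.83 for an odds ratio of 0.48. That is correct, and it limits how serious the point is.

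Two further inferences should not be drawn. One is that the quintiles and the 20-death rule are rerun in each of the six cells formed by neck length and risk. The article attaches the rule to the final primary analysis and does not describe this. The other concerns the British Aneurysm Repair Score, which is used "to divide each comparison group into those that are high risk (the highest risk quartile) and the remainder as standard risk". This could be read as a separate cut-off in each treatment arm. The same section calls the arms intervention groups, so the phrase more naturally means the set of patients being compared, with one cut-off for all arms in it.

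**Conclusion.** The point holds in a limited form. Five strata are out of reach for the pairwise primary comparisons at 2000 patients with equal groups, where usually two or three remain. At 3000 patients, FEVAR against open repair usually keeps three or four when risk varies with propensity. Only strata on the pooled 3000-patient cohort meet the rule comfortably.

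The consequence is more residual confounding than quintiles would leave, with no material gain in precision. The shift in the odds ratio is below 0.5 standard errors under the assumed confounding. It would be wrong to infer that the primary result is invalid or that indication bias returns in full: even two strata remove over 60% of the bias from a normal confounder. The plan should be changed because a better method is available at almost no cost.

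These sizes rest on the assumed EVAR mortality (4% to 8%), roughly equal groups, and a single normal confounder with the slopes stated. A statistical analysis plan that is not shown may name the patients to whom the rule applies. That would settle which row of the tables is relevant, but the adjustment would still depend on observed deaths.

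**What to change.** Delete the 20-death merging trigger. State whether the quintiles are formed on the whole cohort or within each pairwise comparison, and define all five from the propensity score alone, without reference to outcomes. Estimate the common odds ratio by Mantel-Haenszel or by conditional (stratified) logistic regression, both of which remain valid with sparse strata. If the stratified logistic model already planned is the conditional one, only the merging sentence and the definition of the patient set need to change.

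The change is one of wording. Its cost is that some stratum-specific odds ratios in the planned forest plot will be imprecise or not estimable, and a stratum without deaths adds nothing to the pooled estimate. The plot can show such strata with their death counts and mark them as not estimable.
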